## Abstract

**Background**
**:** Issues with questionnaire completion introduce bias and limit examinations in trials. Improving communication with participants about trial processes, such as outcome and questionnaire development, may improve questionnaire completion and response rates. Providing information about the involvement of stakeholders in the development of core outcome sets (COS) measured in trials may improve responding by tapping into subjective norms and behaviour change mechanisms. The aim of this Study Within a Trial (SWAT) is to examine if questionnaire response rates and participants’ attitudes towards questionnaire completion are impacted by providing information about COS use in a trial of a complex intervention.

**Methods:** This is a randomised, single-blinded, parallel group intervention SWAT, embedded within a feasibility trial of an infant feeding intervention to prevent childhood obesity. The SWAT intervention consists of a brief written description and explanation about the development and use of a COS of infant feeding outcomes to prevent childhood obesity, used in the trial. Participants are parents or caregivers of infants aged two months at questionnaire completion. Participants will be randomly assigned to receive the SWAT intervention prior to questionnaire completion (SWAT Intervention), or not (SWAT Comparator). The primary outcome of interest is response rates, which will be measured as proportion of questionnaire completion and individual item response rates. Participants’ attitudes will also be assessed using closed-ended and an open-ended question to evaluate participants’ attitudes about questionnaire completion.

**Discussion:** We hypothesise that providing information about development and use of a COS will increase questionnaire response rates and attitudes toward questionnaire completion relative to the control condition. Findings will indicate the potential usefulness of this strategy for improving participant attitudes and response rates in trials.

**Trial Registration:** This SWAT is registered on the Northern Ireland Hub for Trials Methodology: Research SWAT Repository (
SWAT57).

## Introduction

Evaluation of questionnaire responses is an important dimension of the critical appraisal of health research (
Edwards *et al*., 2009). Incomplete questionnaire responses and participant attrition increase the likelihood of bias and reduce statistical power in trials through reduction of the effective sample size (
Edwards *et al*., 2009;
Fewtrell *et al*., 2008;
Schulz & Grimes, 2002). Further, even in well-designed studies, factors related to research management can influence participant retention and impact questionnaire response rates, leading to research waste (
Al-Shahi Salman *et al*., 2014).

A number of potential methods to effectively increase response rates have been identified, including: the use of monetary incentives, (
Brueton *et al*., 2014); telephone or postal contact with participants prior to questionnaire distribution (
Edwards *et al*., 2009); and personalising questionnaires or survey packs with participants name and/or including a hand-written signature from the principal investigator (
Sahlqvist *et al*., 2011;
Scott & Edwards, 2006). However, reviews have highlighted heterogeneity among strategies used across trials (e.g. differences in the types of incentives used between studies) thus limiting synthesis and conclusions that can be drawn about effectiveness (
Edwards *et al*., 2009). As such, there remains a need to further examine strategies to improve response rates.

Improving communication with participants about aspects related to their trial participation may be one useful strategy. Such communication is posited to enhance participant engagement with research processes in ways that are meaningful to the participant (
Gillies & Entwistle, 2012). For instance, there is some evidence to suggest that participants who feel they are better informed about trial processes tend to have more favourable attitudes toward the trial and are therefore more willing to participate in the trial (
Ellis *et al*., 2001). However, participants and the general public are suggested to have a poor understanding of different aspects of health research (
Ellis *et al*., 1999). This is problematic if it influences participant attitudes and limits engagement with trial processes; there is therefore scope to improve information provision to trial participants.

In terms of enhancing communication to improve questionnaire response rates specifically, one approach may be via providing participants with information about how outcomes are chosen and/or how questionnaires are developed for use in trials. This would be particularly useful where outcomes and questionnaires are developed via engagement with expert stakeholders as is typically done in the development of Core Outcome Sets (COS)(
Williamson *et al*., 2017). COSs are standardised sets of outcomes that represent the minimum outcomes that should be measured and reported in trials for a specific health area or population (
Williamson *et al*., 2012;
Williamson *et al*., 2017). COSs improve evidence synthesis by reducing outcome heterogeneity and reporting risk of bias (
Williamson *et al*., 2012), which have been noted in a range of health areas, including paediatrics (
Gardner & Kelleher, 2017;
Webbe *et al*., 2018), infant feeding (
Whitford *et al*., 2018), and childhood obesity (
[name] *et al*., 2018;
Redsell *et al*., 2016). Expert stakeholders in COS development can include patients, clinicians, trialists, researchers and the public (
Williamson *et al*., 2017). It is suggested that engagement with such stakeholders increases the likelihood that a COS will be relevant and used by these stakeholders in research and practice (
Williamson *et al*., 2017); how engagement of participant stakeholders influences subsequent participant endorsement and use of the COS has not however been fully examined. Knowledge about stakeholder involvement in COS development may influence participant attitudes and response rates via perceptions of subjective norms around the importance of trial outcomes, where stakeholders included are representatives of the participant group. Where COS development involved clinicians and/or practitioners, such stakeholders may be perceived by patient and/or public participants as representing credible sources. This may enhance participant response rates as credible sources have been identified as a useful behaviour change technique (BCT) (
Michie *et al*., 2013), for increasing trial engagement in other trials (
Nyman *et al*., 2018;
Parveen *et al*., 2016;
Redfern *et al*., 2016).

Providing participants with information about COS in trials serves a dual purpose by informing participants about the outcomes of importance being measured in the trial, and highlighting the role of relevant stakeholders in developing the COS being measured in the trial. The influence of informing participants about the development and use of COS in trials on their attitudes towards and completion of trial questionnaires has not yet been examined. This research posits that including information related to COS development and measurement may serve to increase participant knowledge of these processes and/or lead to more favourable attitudes toward questionnaire completion, which would subsequently increase response rates. The aim of this study is therefore to conduct a study within a trial (SWAT) (
Treweek *et al*., 2018a) to examine if provision of information regarding development of a COS influences participants’ questionnaire response rates and attitudes towards questionnaire completion.

## Methods

This SWAT is registered on the Northern Ireland Hub for Trials Methodology Research SWAT Repository (
SWAT57).

### Design

This is a randomised, single-blinded, parallel group intervention SWAT embedded within the Choosing Healthy Eating for Infant Health (CHErIsH) feasibility trial (protocol currently in preparation for submission). The CHErIsH trial involves a brief clinical intervention targeting parents and caregivers to improve infant feeding behaviours between the ages of 0–13 months, delivered during routine primary care-based vaccination visits, alongside an implementation strategy targeted at the healthcare professional (HCP) level to support the delivery of this clinical intervention.

### Study participants

Participants for the SWAT will be the parents or primary caregivers participating in the CHErIsH feasibility trial. The CHErIsH trial participants are recruited from all parents or primary caregivers of infants under 6 weeks of age attending vaccination visits with a participating GP and or practice nurse in the trial site, a primary care centre in the south of Ireland. On average, 450 infants per annum are born to parents attending the primary care centre and during the 3 month recruitment period, it is anticipated that approximately 112 of these will be eligible for recruitment. 

### The Study Within A Trial (SWAT)

The SWAT intervention is a written informational intervention, consisting of a brief written explanation about the COS used in the development of the CHErIsH feasibility trial questionnaires, including the involvement of relevant stakeholders in developing this COS. The COS used is a COS of infant feeding outcomes for inclusion in trials of infant feeding interventions to prevent childhood obesity (
[name] *et al*., 2018a;
[name] *et al*., 2018b). The COS was developed in a four-stage process, involving expert stakeholders in the final three stages (
[name] *et al*., 2017a). Expert stakeholders were parents, HCPs, researchers and childcare professionals.

The SWAT informational intervention will be provided to those randomised, using a random number generator, to the SWAT Intervention group; participants and will be blinded (single blind) to the group assigned (
Figure 1). In the SWAT Intervention, participants will receive the SWAT intervention, in the form of the brief COS information presented at the beginning of the CHErIsH questionnaire at trial baseline (when the infant is less than 2 months old) in the SWAT Intervention. Participants randomised to the SWAT Comparator will receive the information on the COS following completion of both the CHErIsH and SWAT questionnaires; this is to ensure all participants are provided with equal information following questionnaire completion. (
Figure 1).

**Figure 1. f1:**
[figure not shown]
SWAT intervention flowchart.

Information about the COS will be provided to a random sample of half of all participants at the beginning of the CHErIsH Questionnaire in a brief paragraph including the following:

A statement that the questionnaires include measurement of outcomes from an infant feeding COS.A lay-summary of what a COS is and how COSs can improve examination of trial outcomes informed by the Core Outcome Measures in Effectiveness Trials (COMET) Initiative COS lay summary (
COMET, 2018).A brief description of how the infant feeding COS was developed with experts, including parents of infants and HCPs.

The included SWAT Intervention text is as follows:

This questionnaire includes questions about infant feeding that were put together as part of a core outcome set. Core outcomes sets are a group of outcomes (related to questions in a questionnaire) that should be measured in all studies in a health area. They are important because they allow researchers to bring together findings from many different studies to give us a better understanding about what works and what doesn’t. This improves the quality of information and helps us develop and examine better healthcare programmes and strategies.

Parents of infants, healthcare professionals, researchers, and childcare professionals decided the questions included in this questionnaire as part of the core outcome set process. This means the questions have been decided by people, including parents like you, to help us best measure how people feed their babies.

### Outcome measurement

The primary outcome of interest is the proportion of questionnaire completion. Individual item response rates will also be assessed in terms of completion of questions on infant feeding outcomes, and other outcomes such as healthcare utilization and parent well-being. This is because the SWAT Intervention text specifically refers to infant feeding, and so this study will examine whether the intervention influenced completion of these outcomes specifically.

A secondary outcome of interest is participant attitudes about questionnaire completion. Data on participant attitudes will be collected via questions included at the end of the CHErIsH questionnaire; the CHErIsH questionnaire can be completed online, in-person, or by phone based on participant preference, and so the SWAT questions can be similarly completed. Quantitative data for participant attitudes will be collected for all participants using the following two questionnaire items, which are rated from on a 5-point Likert scale from ‘strongly disagree’ to ‘strongly agree’:

1. The infant-feeding related questions in the questionnaire were useful for gaining insight into how you feed your child.2. The infant-feeding related questions in the questionnaire were appropriate for gaining insight into how you feed your child

Participants in the SWAT Intervention group will also be asked the following two questions, the first of which is closed-ended and rated from on a 5-point Likert scale from ‘strongly disagree’ to ‘strongly agree’. The second SWAT Intervention question is a single open-ended question that allows participants to describe in their own words how the information on COS influenced their completion of the questionnaire. Both questions are as follows:

3. The information provided about Core Outcome Sets (COSs) influenced my completion of the questionnaire.4. How did the information about Core Outcome Sets (COSs) influence your completion of the questionnaire?

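### The attitude outcome is labelled as attitude to completing the questionnaire, but the only items asked in both arms rate the infant-feeding questions

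*Protocol article*

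**What the plan says.** The hypothesis in the Abstract is comparative: "providing information about development and use of a COS will increase questionnaire response rates and attitudes toward questionnaire completion relative to the control condition". Outcome measurement uses the same construct: "A secondary outcome of interest is participant attitudes about questionnaire completion". The Discussion of the article lists as a strength that the closed items let attitudes to completion be evaluated in both conditions.

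Outcome measurement prints the items in full. For both arms: "Quantitative data for participant attitudes will be collected for all participants using the following two questionnaire items". Item 1 is "The infant-feeding related questions in the questionnaire were useful for gaining insight into how you feed your child" and item 2 is "The infant-feeding related questions in the questionnaire were appropriate for gaining insight into how you feed your child", each on a 5-point agreement scale.

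Then: "Participants in the SWAT Intervention group will also be asked the following two questions". Item 3 (closed) asks whether the COS information influenced completion, and item 4 (open-ended) asks how. The Analysis section summarises item 3 descriptively and rules out inferential statistics because it comes from one arm. Item 4 is analysed thematically.

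The intervention text, shown at the start of the questionnaire in one arm, says the questions were decided by people including parents "to help us best measure how people feed their babies". The comparator arm sees this text only after both questionnaires are finished.

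**The concern.** The hypothesis is about one thing and the shared items ask about another. Attitude to completing a questionnaire would cover matters such as willingness, burden, or whether answering seemed worthwhile. Items 1 and 2 instead ask whether one block of questions was a good way of learning how the respondent feeds the child. A parent could rate the feeding questions highly and still find the questionnaire tedious, or the reverse.

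What is at stake is the conclusion attached to the data. The Introduction posits a route from information, through more favourable attitudes to completion, to higher response. If items 1 and 2 differ between arms, the plan's own labels would have this reported as support for the middle step of that route. If they do not differ, the same labels would have it reported as evidence against. Neither inference follows directly from what was asked.

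**Working it through.** There is no arithmetic beyond a count. The article gives no effect size, standard deviation or power for the attitude outcome, so no numerical size can be derived. The check sets hypothesis, items, arms and intervention text side by side.

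**Step 1. What each item covers** (Outcome measurement; Analysis)

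| Item | Asked of | What it is about | Mentions completion? | Between-arm comparison possible? |
|---|---|---|---|---|
| 1 | Both arms | Usefulness of the feeding questions | No | Yes |
| 2 | Both arms | Appropriateness of the feeding questions | No | Yes |
| 3 | Intervention only | Whether COS information influenced completion | Yes | No |
| 4 | Intervention only | How COS information influenced completion (open-ended) | Yes | No |

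Items that mention completion: 2 of 4. Items that can be compared: 2 of 4. Items that do both: 0 of 4. Items 1 and 2 are worded alike apart from one adjective, so the second does not widen the subject matter beyond the feeding questions.

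**Step 2. Could items 3 and 4 fill the gap?** Not for the hypothesis as worded, which is relative to control. They refer to information that the comparator arm has not seen when it answers, so they could not be asked there in the same form. Item 3 also has no direction: agreeing that the information had an influence does not say whether the influence was favourable.

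**Step 3. How much of the questionnaire do items 1 and 2 cover?** Outcome measurement says the questionnaire also asks about healthcare utilisation and parent well-being. Items 1 and 2 are confined to the feeding questions, while the hypothesis and outcome refer to the questionnaire as a whole.

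**Step 4. Overlap with the intervention text.** The text tells one arm that the questions were chosen "to help us best measure how people feed their babies". Items 1 and 2 then ask whether those questions give insight into how the respondent feeds the child. The overlap is in content, not wording: the text uses neither of the two adjectives. Higher agreement in the intervention arm could reflect a changed view of the questions, acceptance of a statement read earlier, or both. The design does not separate these.

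**The case against.** The best defence is that items 1 and 2 follow from the article's rationale. The Introduction argues that COS information may work through perceived norms about which outcomes matter and through credible sources. Seeing the questions as useful and appropriate is a plausible early step on that path. The feeding focus is deliberate, because the intervention text is about infant feeding and item response is examined for those questions specifically. This stands, and it makes the two items a reasonable proxy. It does not make them a measure of attitude to completion.

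A reader might infer that the hypothesis cannot be tested at all. The documents do not support that: items 1 and 2 are designated as the attitude measure for all participants and can be compared between arms, so an indirect test exists.

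A reader might also infer that any difference on items 1 and 2 would merely repeat the intervention text. That also goes too far. The text comes at the start of the questionnaire and the items at the end, the wording differs, and an information intervention is meant to change beliefs about the questions. The size of any such effect cannot be derived from the article. The overlap is a reason for caution in interpretation, not proof of bias. A new self-report item on completion would not be free of this problem either.

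Nor is the plan silent on mechanism. Item 4 asks the intervention arm directly how the information affected completion, which gives some qualitative evidence.

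Finally, the article may condense a fuller plan. That does not help here, because the items and the arms that receive them are printed in full, and an analysis plan cannot change what participants were asked.

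**Conclusion.** The point holds as a mismatch between label and measurement. The hypothesis, the secondary outcome and the strength claimed in the Discussion all refer to attitudes to completing the questionnaire in both arms. What is measured in both arms is perceived usefulness and appropriateness of the infant-feeding questions. A between-arm difference on items 1 and 2 is indirect evidence at most and does not by itself show improved attitudes to completion.

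Its reach is limited. It concerns a secondary outcome in a study within a feasibility trial, and the primary outcome, questionnaire completion, is untouched. It should be corrected because the correction is cheap and the present labels invite an unsupported conclusion. The verdict assumes that the items printed in the article are those in the SWAT questionnaire posted as extended data, which is not shown here.

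**What to change.** Either of two changes would do.

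1. **Relabel.** In the Abstract, Outcome measurement and the Discussion, restate the secondary outcome and hypothesis as perceived usefulness and appropriateness of the infant-feeding questions. Draw no between-arm conclusion about attitudes to completion from items 1 and 2. This costs only wording, and gives up the completion-attitude claim.

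2. **Add or swap one item.** Study status and Data availability say the study had not yet begun. Ask both arms one brief item about completing the questionnaire, on the same 5-point scale and without mentioning the COS. For example, ask whether completing it was a worthwhile use of the respondent's time. Use that item for the completion-attitude hypothesis and describe items 1 and 2 as ratings of the feeding questions. The cost is one extra item, or the loss of one of the two similar ratings, together with a revision of the posted SWAT questionnaire and a probable notification to the ethics committee, whose approval is already in place.

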### Analysis

*Quantitative analysis*: All questionnaire data will be entered into SPSS Version 24 software. Questionnaire response rates will be calculated for each of the SWAT Intervention and SWAT Comparator including proportion of completion of the CHErIsH questionnaire and individual item response rates. Chi squared tests will compare the proportion of the questionnaire completed for the two conditions. Potential differences between participant baseline characteristics (age, sex, education) will also be examined and should differences be observed, these will be controlled for using logistic regression.

Data from the SWAT Intervention group in response to the question 3 will be descriptively summarised in terms of participants’ mean attitude rating, standard deviation and range of ratings. As this data is only collected from the SWAT Intervention, inferential statistics will not be conducted.

*Qualitative analysis*: Responses to the open-ended question will be entered into NVivo 12 for qualitative data management and will be analysed using thematic analysis following Braun and Clarke (2006) guidelines. This will involve an iterative process of reading and re-reading the data, developing initial line codes, followed by categorisation and development of themes. However, if there is insufficient detail in the open-ended responses then they will be examined narratively.

